## Abstract

**Background:**

Depression guidelines in the UK recommended a policy of watchful waiting for mild depression due to a lack of evidence for the effectiveness of antidepressant treatment for mild cases. However there has been relatively little research carried out in primary care to help establish the severity threshold at which antidepressant treatment is effective and cost-effective.

**Methods/Design:**

The THREAD (THREshold for AntiDepressants) study is a multi-centre randomised controlled trial designed to determine the clinical and cost effectiveness of a selective serotonin reuptake inhibitor (SSRI) plus general practitioner (GP) supportive care, versus supportive care alone, for mild to moderate depression in primary care. The aim is to recruit 300 patients from three centres (Southampton, London and Liverpool). Depressive symptoms will be assessed at baseline, 12 weeks and 26 weeks, using the 17-item Hamilton Depression Rating Scale (HDRS). Two severity sub-groups of patients will be recruited, with HDRS scores of 12–15, and 16–19. Possible predictors of response will be explored including life events and difficulties and alcohol consumption. Analysis of covariance, controlling for baseline value, severity group and centre will be used to estimate the overall treatment effectiveness (difference in HDRS score) at final follow up. The primary analysis will be by 'intention to treat' using double sided tests. The interaction between severity sub-group and treatment will be tested, and if appropriate, effects within separate severity sub-groups estimated. The economic analysis will compare the two treatment groups in terms of mean costs and cost-effectiveness.

**Discussion:**

The results of this study will give GPs important information to help them determine the severity of depression at which antidepressant treatment is likely to be cost-effective.

## Background

### Increasing prescribing of antidepressants – is it appropriate?

Prescribing of antidepressant drugs has increased by 36% over the last 5 years to around 30 million items (7.3 million in the quarter to June 2005), and the cost has increased by 20% to around £380 million (£91 million for the same quarter) [1].

However, much of this increased prescribing may be inappropriate. As a result of the perceived pressure to treat more depression, antidepressants are being prescribed more frequently for depressive symptoms below the threshold for major depression [2]. Clinical guidelines recommend antidepressant medication as first-line treatment for patients meeting diagnostic criteria for major depressive disorder [3,4]. Antidepressants are not recommended for the initial treatment of mild depression because the risk-benefit ratio is considered to be poor. However, these guidelines have been produced based largely on consensus or expert opinion. There has been relatively little research in primary care on which to base recommendations on the threshold at which antidepressants should be offered. Studies in primary care have shown that antidepressants are more effective than placebo or treatment as usual for probable major depression but results have been mixed for minor (mild) depression.

### Previous research in primary care

A general practice based placebo-controlled trial of amitriptyline found that patients with probable major depressive disorder benefited from drug treatment, but those with minor depression did no better on them than on placebo [5]. However these findings represent a post-hoc analysis of responses in the two sub-groups of patients who did or did not fulfil criteria for a diagnosis of probable major depression. The study was not set up specifically to assess the relationship between severity and response to treatment.

A placebo-controlled trial of the SSRI paroxetine, versus problem-solving, versus non-specific clinical management or 'watchful waiting' for minor depression and dysthymia in a primary care population was undertaken in the USA [6]. The results were mixed: among patients aged 18 to 59 years with dysthymia, paroxetine improved remission compared with placebo plus non-specific clinical management, while for minor depression they were equally effective [7]. Among patients aged 60 and over paroxetine was beneficial in dysthymia and among more severely impaired patients with minor depression [8]. The authors suggested that 'watchful waiting' i.e. supportive care but without the prescription of antidepressants, was an appropriate treatment option for minor depression, at least in adults and in elderly patients with mild impairment.

Judd et al [9] carried out a randomised placebo controlled trial of fluoxetine among 162 patients with minor depressive disorder and found that fluoxetine was better in terms of clinical effectiveness in terms of the Hamilton Depression Rating Scale (HDRS). The mean difference was only one point on the HDRS. Minor depression in these subjects was primarily characterised by mood and cognitive symptoms, not the classical neurovegetative signs and symptoms. One third had a past history of major depressive disorder, however HDRS scores at baseline ranged from 6–21 inclusive, on the 17 item scale [10].

Finally, most recently, Perahia et al [11] found that duloxetine was more effective than placebo in 159 patients with milder major depressive disorder (HDRS scores on the HAMD17 between 15 and 18 inclusive) over 9 weeks. The mean different was relatively small, 2.9 points on the HDRS. However, this was a post-hoc sub-group analysis of pooled data from two trials.

There is evidence that one form of mild depression, dysthymia, responds to antidepressants. Dysthymia is a term used to describe chronic low-grade depression and in ICD-10 requires that four or more depressive symptoms are present for at least two years [12]. A recent systematic review and meta-analysis suggested that antidepressant drug treatment is effective in the management of dysthymia, but the research studies analysed were conducted in secondary care settings [13].

### Predictors of response

The placebo-controlled trial of amitriptyline in general practice referred to above found no difference between those categorised as having endogenous and non-endogenous depression. The authors recommended drug treatment for major depression, regardless of demographic characteristics, a past history of depression, or the presence or absence of endogenous features [14]. These findings have led to recommendations to prescribe drug treatment for depression if symptoms are severe enough, and functioning is impaired, even if there seems to be an understandable cause for depression such as adverse events or continuing difficulties in the patient's life [3,15-17]. However, the importance of social factors in depression is undeniable, and there is substantial evidence to suggest that both onset and recovery are related to life events and difficulties.

Depression is strongly associated with lower socioeconomic status [18,19], poverty [20], unemployment [19,21], separation or divorce [18,22], and poor housing [23]. Predisposing factors among women include demanding child care [24], lone motherhood and poor social support [25]. A lower severity of premorbid difficulties has been shown to be associated with a reduced time to remission, at least among patients with high self-esteem and better coping strategies [26]. Recovery from depression is related to positive social support and life events which can be perceived as 'fresh starts', which may or may not be related to the original adverse events and difficulties associated with onset [27]. A reduction in marked social difficulties has been found to predict recovery from depression among patients in primary care [28] whereas recognition and drug treatment by the general practitioner has not [29,30].

The scant research into psychosocial predictors of response carried out so far in secondary care suggests that greater emotional support, and a relative lack of experience of adversity, particularly in domains of the patient's life which are regarded as most important, are more strongly related to recovery than drug treatment [31]. As findings in secondary care may not generalise to primary care however, more research is needed to determine whether such social and cognitive factors predict response to drug treatment in a primary care setting.

In general somatic presentations of depressive disorder are associated with reduced severity of depressive symptoms but similar impairments in function and a similar prognosis [32]. However, it is important to go on to explore whether the number of physical symptoms affects treatment responses when comparing drug and non-drug treatments.

### The need for a new study

The US studies described above compared SSRIs to placebo and were therefore efficacy trials which cannot establish cost-effectiveness in practice. Also, findings from the USA may not generalise to primary care in the UK, as the type of supportive care usually provided in the UK, which may include referral to a practice counsellor, differs from the 'watchful waiting' provided in the US study. If SSRI treatment is effective in mild depression, its cost-effectiveness needs to be established within the UK health care system. Predictors of response to antidepressant treatment also need to be identified, to help practitioners decide which patients should be offered them.

The THREAD study is designed to inform guideline recommendations by exploring in general practice whether the added prescription of a SSRI antidepressant is more cost-effective than support from the GP alone in patients with mild to moderate depression.

Our research questions are:

1. Is treatment with a SSRI plus supportive care more effective and cost-effective than supportive care alone?

2. If it is more effective, does this apply across the whole range of severity of symptoms of mild to moderate depression?

3. What patient factors might predict a beneficial response?

The hypothesis is that SSRI treatment will be more effective and cost-effective than supportive care alone among patients scoring 16–19 on the Hamilton Rating Scale (HDRS) but not among those scoring 12–15.

We will also explore the impact of a number of predictors on the outcome in the two treatment arms, namely demographic and social variables, alcohol consumption, physical symptoms, recent life events and difficulties, the patient's self-rating of the cause of their illness, and the duration of their depressive symptoms.

## Methods/Design

### Trial design

The study is a randomised controlled trial that compares treatment with a SSRI plus supportive care, versus supportive care alone, over 26 weeks follow-up. The aim is to establish the clinical and cost effectiveness of SSRI antidepressants added to GP support over GP support alone, in clinical practice conditions. It is not an efficacy study and there is no placebo control group (placebos are not given in clinical practice and cannot be costed into the economic analysis).

### Ethical approval

Ethical approval was gained from the West Midlands Multi-Centre Research Committee (MREC) (reference number: 02/7/091).

### Setting

Patients are being recruited from general practices around three centres: Southampton, London (co-ordinated by the Institute of Psychiatry and Kings College London), and Liverpool.

### Patients

#### Inclusion criteria

Patients are eligible for inclusion if they are aged 18 and above, and are found to be depressed by their GPs and potentially in need of treatment. Patients must have at least one somatic symptom on the Bradford Somatic Inventory [33]. Only patients for whom the likely benefit of treatment is uncertain in the mind of the GP are referred to the study because it is essential that the GP is in equipoise about the likely outcome. To avoid including patients with more transient depression, they need to have had symptoms for at least eight weeks. To include only patients with new episodes of depression, they must not have received treatment for depression within the previous 12 months.

#### Exclusion criteria

Patients are excluded from the study if:

• they are found to have an HDRS score of less than 12, or greater than 19

• they suffer from suicidal intent

• they report significant substance misuse, determined using screening questions

• if they score 13 or more on the Alcohol Use Disorders Identification Test (AUDIT) questionnaire

• they do not have the spoken or written language skills necessary to take part

Figure 1 shows the procedure of what is involved for the patients recruited into the study.

**Figure 1 F1:**
[figure not shown]
**Trial design**. Flow chart to show the study procedure.

### Interventions

#### Supportive care alone

The GP is asked to see the patient for support in follow-up appointments at 2, 4, 8 and 12 weeks after they have been randomised into the study. They are asked to refrain from prescribing antidepressants during this 12 week period. However, if the patient deteriorates and the GP feels that they are in need of antidepressants then they can be started on drug treatment. If this does occur then the patient can continue in the study but remains in the support alone arm on an intention to treat basis.

#### SSRI antidepressant plus supportive care

The patient is prescribed an appropriate SSRI and then seen by the GP at the times listed above. The GP is also at liberty to switch SSRIs should the initial choice prove unsuitable. The GP is advised to continue treatment for four months after recovery but it is stressed to the GP that this is a pragmatic study and that they should use their clinical judgement in relation to the duration of the patient's treatment.

The GPs are free to refer patients in either arm for counselling or psychological therapy if this is appropriate in their judgement, but waiting times for counselling and psychological treatment are such that patients will not usually receive this before the 12 week follow-up, and so this will not affect the comparison for the primary outcome.

### Randomisation

Block randomisation with random block sizes, stratified by severity sub-group and centre, is carried out by an independent centre (The Institute of Psychiatry Clinical Trials Unit) over the telephone.

### Blindness

The researchers carrying out the interviews are kept blind to the treatment arm, if possible. Patients are asked not to reveal whether or not they have been prescribed antidepressants prior to the follow-up interviews. All instances of unblinding are recorded.

### Patient assessments

The initial assessment takes place at baseline with follow up interviews being carried out at 12 and 26 weeks after randomisation. Table 1 summarizes the measures that are used at each point.

**Table 1 T1:** Summary of measures

**Measure**	**Baseline**	**12 week follow-up**	**26 week follow-up**
17-item Hamilton Depression Rating Scale Interview (HDRS)			
Sociodemographic questionnaire			
AUDIT measure of alcohol consumption			
Beck Depression Inventory (BDI-II)			
Date of onset questionnaire			
Short Form 36 (SF36) – health-related quality of life measure			
Bradford Somatic Inventory (BSI)			
Short Life Events and Difficulties Schedule (S-LEDS)			
Symptom attribution questionnaire			
Patient expectations questionnaire			
Client Service Receipt Inventory (CSRI)			
Patient Satisfaction Scale			
Measure of Care Received questionnaire			

A summary of which measures are collected from the patients at each time point during their participation in the study.

### Outcome measures

The primary outcome measure is the 17-item HDRS score at 12 weeks. The BDI-II, the SF-36, the Patient Satisfaction Scale and the HDRS at 26 weeks are all secondary outcomes. The sociodemographic, duration of depression, alcohol consumption, somatic symptom inventory, LEDS and symptom attribution measures are all potential predictors of response.

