### Sample size

The sample will be divided into two severity sub-groups (HDRS scores 12–15 and 16–19). Hollyman *et al *found the standard deviation (SD) of the HDRS to be around 3.5, and reported roughly similar numbers of patients in these two severity ranges [43]. We assume this SD, equal numbers in the two sub-groups, a pre-post correlation of 0.5, and significance level of 0.05.

Using analysis of covariance controlling for baseline values, 49 patients at follow-up in each treatment/severity combination will allow the following effects to be detected (standard effect sizes in brackets): an overall average difference in HDRS score of 1.4 (0.4) with 90% power; an interaction (difference between effects in the two severity sub-groups) of 2.5 (0.7) with 80% power; and a difference between treatment arms within the more severe group of 2.0 (0.6) with 90% power. The latter two calculations are conservative (tending to underestimate the power) because the SDs may be lower within the severity subgroups. A difference of 1.4 on the HDRS is a relatively small difference (0.4 standard deviations) and any difference smaller than this we regard as clinically insignificant. In the trial of amitriptyline by Hollyman *et al *the HDRS scores fell by a mean of around 10 points in the mildly depressed group and around 13 in the more severely affected group [43]. Therefore the sample size should be sufficient to detect clinically significant differences.

One hundred and ninety six patients will therefore need to be followed up to detect these differences (98 in each of the two arms). To allow for up to 25% loss to follow-up at 12 weeks, 261, 87 at each of the three sites, would be needed. The aim is to recruit 300, 100 at each site.

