### Analysis

Analysis of covariance, controlling for baseline value, severity sub-group and centre will be used to estimate the overall treatment effectiveness (difference in HDRS score) at follow up. The primary analysis will be by 'intention to treat' using double sided tests. The interaction between severity sub-group and treatment will be tested, and if appropriate, effects within separate severity sub-groups estimated. Further exploratory analyses will also assess the impact of other explanatory factors and will also model the time course of effects using the 12-week measurement in a panel analysis. Sensitivity analyses will include estimating 'on treatment' effects and CACE (complier average causal effects), and by imputation of any missing values.

The main aim of the economic analysis is to compare the two treatment groups in terms of mean costs and cost-effectiveness. A secondary aim is to examine differences between the sub-groups defined by severity. Cost data are frequently skewed and this can cause a violation of the assumptions of standard significance tests. In the event of this, bootstrapped estimates (multiple re-sampling within treatment arms) will be determined, whereby mean costs can still be compared whilst imposing no prior assumptions regarding the data distribution. To explore cost-effectiveness, a net benefit variable will be generated which synthesises data on costs and outcomes, also analysed by bootstrapping.

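### The named primary outcome (HDRS at 12 weeks) and the described main analysis disagree on the time point

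*Protocol article*

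**What the plan says.** Three sections of the protocol article point to 12 weeks.

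- **Outcome measures:** "The primary outcome measure is the 17-item HDRS score at 12 weeks". In the sentence that follows, the BDI-II, the SF-36, patient satisfaction and "the HDRS at 26 weeks are all secondary outcomes".
- **SSRI antidepressant plus supportive care:** on counselling and psychological therapy, the article argues that "patients will not usually receive this before the 12 week follow-up, and so this will not affect the comparison for the primary outcome".
- **Sample size:** "To allow for up to 25% loss to follow-up at 12 weeks, 261, 87 at each of the three sites, would be needed".

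Two places describe the main analysis.

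- **Abstract, Methods/Design:** analysis of covariance, controlling for baseline, severity group and centre, "will be used to estimate the overall treatment effectiveness (difference in HDRS score) at final follow up". Patient assessments has "follow up interviews being carried out at 12 and 26 weeks after randomisation", so the last follow-up is at 26 weeks.
- **Analysis:** the same model is to "estimate the overall treatment effectiveness (difference in HDRS score) at follow up", with no week given. Further exploratory analyses "will also model the time course of effects using the 12-week measurement in a panel analysis".

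**The concern.** A trial's main test should be run on its named primary outcome. Here the outcome section gives one time point, the abstract gives the other for the main model, and the Analysis section leaves it open.

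The choice of week is not a formality, because the design treats the first 12 weeks differently from the rest:

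- The Supportive care alone section asks GPs to hold back from prescribing antidepressants for the first 12 weeks only.
- The argument that counselling will not disturb the primary comparison rests on waiting times outlasting the 12-week visit. It does not carry over to 26 weeks.
- The 25% allowance for loss is for 12 weeks. No loss is stated for 26 weeks.

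The two time points can therefore measure different treatment contrasts. If the week is left unsettled, the choice could be made after the results are known.

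**Working it through.** **1. The passages side by side**

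| Place in the article | Time point it supports | Explicit or implied |
|---|---|---|
| Outcome measures | 12 weeks primary, 26 weeks secondary | Explicit |
| SSRI plus supportive care (counselling) | 12 weeks | Explicit link to the primary outcome |
| Sample size (loss to follow-up) | 12 weeks | Explicit for the loss only |
| Abstract, ANCOVA | 26 weeks | Explicit, read with the visit schedule |
| Analysis, ANCOVA | None named | – |
| Analysis, panel model | 26 weeks for the main model | Implied |

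The last row is an inference. If the main ANCOVA were already at 12 weeks, a time-course model would need the 26-week score added to it. The article describes adding the 12-week score, which fits most naturally with a main model at 26 weeks.

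**2. The article's own sample size**

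Inputs from Sample size: SD 3.5, pre-post correlation 0.5, significance level 0.05, 98 per arm, 49 per treatment/severity cell. Two-sided tests are stated under Analysis.

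- Residual SD = 3.5 × √(1 − 0.5²) = 3.031.
- Overall effect: SE = 3.031 × √(2/98) = 0.433. Power for 1.4 = Φ(1.4/0.433 − 1.96) = 89.9% (stated 90%). Solving for n gives 99 per arm (stated 98).
- Interaction: SE = 3.031 × √(4/49) = 0.866. Power for 2.5 = 82% (stated 80%).
- More severe group: SE = 3.031 × √(2/49) = 0.612. Power for 2.0 = 90.4% (stated 90%).
- Loss: 196/0.75 = 261.3 (stated 261).

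All reproduce within rounding. The formula itself fixes no week; only the 25% loss is tied to 12 weeks.

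**3. Margin if 26 weeks were used**

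With 300 recruited and 196 needed, tolerable loss = 1 − 196/300 = 34.7%. The article gives neither loss nor correlation for 26 weeks. Under assumed values, with n per arm = 300 × (1 − loss)/2, power for 1.4 points is:

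| Assumed loss | Assumed correlation | n per arm | Power |
|---|---|---|---|
| 25% | 0.5 | 112.5 | 93% |
| 35% | 0.5 | 97.5 | 90% |
| 35% | 0.4 | 97.5 | 86% |
| 40% | 0.3 | 90 | 80% |

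**4. Illustration: a smaller contrast at 26 weeks (assumed)**

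If the 1.4-point effect shrank by 10%, 20% or 30% (to 1.26, 1.12 or 0.98), with SD 3.5 and correlation 0.5, power would be:

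- at 98 per arm (SE 0.433): 83%, 73%, 62%;
- at 112.5 per arm (300 recruited, 25% loss; SE = 3.031 × √(2/112.5) = 0.404): about 88%, 79%, 68%.

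**5. Illustration: either week claimed as primary (assumed)**

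With two tests at 0.05 each, the chance of at least one false positive is 1 − P(|Z₁| < 1.96 and |Z₂| < 1.96). This is 1 − 0.95² = 9.75% if the tests are independent, and 9.1%, 8.3% or 7.0% for assumed correlations of 0.5, 0.7 or 0.9.

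**The case against.** The best defence is that the article does name one primary outcome and ranks the 26-week score below it, with the counselling argument and the loss allowance in agreement. The only explicit contrary statement is a phrase in the abstract. On this view the Analysis section simply means the primary time point, and the panel sentence reuses the 12-week data.

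Much of this stands. A reader might infer that the trial has no single primary result; the explicit ranking in Outcome measures does not support that. A reader might also take the Analysis section as fixing the main model at 26 weeks; it suggests so but names no week.

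Nor do the documents show that a 26-week analysis would lack power for its own attrition. Recruiting 300 tolerates about 35% loss and still leaves 196. All that can be said is that no 26-week loss is given.

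A smaller contrast at 26 weeks is plausible but not certain. GPs may already start antidepressants in the support arm before 12 weeks if the patient deteriorates, and counselling is only said to be unusual by then, so the two time points differ in degree.

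The defence does not remove the contradiction itself. The abstract and the outcome section are both current text, they disagree, and the Analysis section, which should settle the matter, leans towards the abstract. This is a conflict in what is stated, not detail left to an analysis plan.

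**Conclusion.** The point holds as an internal contradiction about the time point of the main analysis. The abstract's ANCOVA is on a variable that the article classes as secondary, and the Analysis section does not correct it. It should be settled because it decides which variable carries the confirmatory test.

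Its size cannot be given as one number. The sample size calculation is sound and does not change when 12 weeks is named. The power figures for 26 weeks depend on loss, correlation and dilution values that the article does not give. The type I error of about 8–9% (correlations 0.5 to 0.7) applies only if the stated ranking were disregarded and either week claimed as primary; it is not the error rate of the plan as ranked.

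**What to change.** - In the abstract and in the Analysis section, state the primary analysis as ANCOVA of HDRS at 12 weeks on treatment arm, baseline HDRS, severity sub-group and centre.
- Label the same ANCOVA at 26 weeks as secondary.
- Reword the panel analysis so that it adds the 26-week measurement to the 12-week one.

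Twelve weeks is the week to name because Outcome measures, the counselling argument and the loss allowance already rest on it. The cost is a few words in two places, to be settled before outcomes are compared by arm. No patients, data or new sample size calculation are needed.
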